## Abstract

**Background:**

Practising target-shooting sport requires focused attention and motoric steadiness. A previous non-controlled pilot study suggests that children with impairing symptoms of attention-deficit/hyperactivity disorder (ADHD) benefit from participating in target-shooting sport in local shooting associations, as rated by parents and teachers.

This study aims at examining if, and to which extent, target-shooting sport reduces parent- and teacher-reported severity of inattentiveness, hyperactivity, and impulsivity in children with attention difficulties, and if, and to which extend, target-shooting sport improves the children’s wellbeing and quality of life.

**Methods:**

A mixed method approach is applied. A non-blinded, waiting list controlled study is combined with a case study, consisting of interviews and observations. The intervention consists of children practising target-shooting sport, by attending a local shooting association, once a week for six months, during regular school hours. Data from questionnaires (ADHD-RS, SDQ, Kidscreen-27), as well as a computerized continued performance test (Qb test), measure the children’s activity and attention. The study includes 50 children in an intervention group and 50 children in a waiting list control group. The Qb test collects data from at least 20 children from the intervention group and at least 20 children from the waiting list control group. Data from the questionnaires and Qb-test is collected at baseline, and six months post intervention. In addition, a case study is carried out, consisting of interviews of at least five children from the intervention group, their parents, teachers and shooting instructors. Observations are carried out, when children are in school and while they are attending the local shooting association. The case study adds to an in-depth understanding of children’s participation in target-shooting sports.

**Discussion:**

At present, little is known about the effects and influence of practising target-shooting sport for children experiencing difficulties with inattentiveness, hyperactivity and impulsivity. This study is expected to contribute to an understanding of the influence of participating in target-shooting sports on inattentive, hyperactive and impulsive symptoms, and the effects on the children’s psychological wellbeing and quality of life.

**Trial registration:**

Current Controlled Trials NCT02898532. Retrospectively registered 14 September 2016.

## Background

Children diagnosed with attention-deficit/hyperactivity disorder (ADHD) (DSM-5) are characterized by three core symptoms: inattention, hyperactivity and impulsivity [1]. Approximately 2–3% of children attending Danish schools are diagnosed with ADHD [2, 3], and worldwide the population prevalence of ADHD is 5% [4]. Many children with ADHD experience difficulties in managing social relations, and are often excluded from participating in leisure activities with other children, e.g. team sports [5]. This may have negative impacts on their wellbeing and quality of life, which depend on having friends and relationships with peers [5]. Between 25 and 50% of those with childhood ADHD experience persisting symptoms and impairment in adulthood, and many develop psychological and social problems [6] and are at risk of premature death [7]. The NICE guideline [8] recommends a combination of pharmacological and psychosocial treatment (multimodal treatment approach) for children aged 6–18 years, to remedy symptoms of both ADHD and comorbid disorders. A growing focus on the benefits of sports activities, yoga and mindfulness suggests that physical activity may have a positive impact on children and young people, also those with ADHD [9–13].

Target-shooting sport may be regarded as mental training, where the participant uses breathing techniques to calm down and focus, and thereby improves attention. Mind and body must be in complete balance during practice. These techniques are somewhat similar to those used in meditation [14]. The Danish Shooting Association has nationwide standards and regulations, which must be adhered to by all participants practising and instructing target-shooting sports. These clear guidelines and boundaries have several characteristics, which may be beneficial for children, with ADHD. While at the shooting range, the children practice in separate, individual cubicles. They use earmuffs to protect their hearing. Furthermore, each child receives guidance and supervision from an individual adult instructor. The instructor will be standing next to the child at all times. It is custom for the instructor to give instructions in a calm, structured and concise manner. Finally, when practising target-shooting sport, the children receive immediate feedback on their performance, in terms of whether they hit the target or not. Thus, target-shooting sports has per se elements, similar to elements in behavioural interventions often directed at children with ADHD or oppositional defiant disorder/conduct disorder. In addition, the sport has elements of mental training, which may contribute to reducing ADHD-symptoms, and comorbid symptoms, and participating in a sport without requiring additional help or guidance, compared to children without ADHD, may strengthen the child’s wellbeing and self-perceived quality of life. In 2012, DGI Shooting (A large sports organization in Denmark) initiated a sport project, where children with ADHD or sub-threshold symptoms of inattention, hyperactivity and impulsivity practiced target-shooting sports in local shooting associations, during regular school hours. The sport project was initiated as a collaboration between DGI Shooting, local shooting associations and local schools. The evaluation showed, that participating children increased their concentration-span and focus during the training, and the children had valuable experiences of success, when practising the sport. Some of the children also returned to the local shooting associations in their spare time, and thereby participated in leisure activities with children outside the sport project [15]. This study has been based on these preliminary findings. To the best of our knowledge, no previous controlled trial has investigated the effects and influence of practising target-shooting sport, for children with difficulties with inattention, hyperactivity and impulsivity. The main aim of this study is therefore to investigate the influence of participating in target-shooting sports in Danish Shooting Associations, as an intervention for children exhibiting difficulties with inattention, hyperactivity and impulsivity, on symptoms of ADHD and comorbid symptoms and on quality of life.

## Methods and design

A mixed method approach is used in a pre-post design [16] (Fig. 1) combining a case study [17] with a multiple informant survey and a computer test of the children’s performances.

**Fig. 1 Fig1:**
[figure not shown]
Flow Diagram (Inspired of CONSORT 2000)

### Objectives

The study will investigate beneficial and adverse effects of the intervention on children’s:

Inattention, hyperactivity, and impulsiveness.

Comorbid symptoms, such as emotional, social and behavioural difficulties.

Well-being and quality of life.

We hypothesise, that participation in the target-shooting sports in local Danish shooting associations, will reduce the children’s symptoms of inattention, hyperactivity and impulsivity, their comorbid symptoms, and enhance their wellbeing and self-reported quality of life.

### Participants

Inclusion: Children aged 10–14, meeting the following criteria: either a clinical diagnosis of ADHD or rated by school staff or school psychologist to have impairing difficulties with inattention, hyperactivity and impulsivity, affecting the child’s school attendance. Included schools are either, schools for children with special needs or municipal schools with special educational programmes for children diagnosed with either ADHD or severe and impairing difficulties of hyperactivity, inattention and impulsivity. If the child receives pharmacological treatment for ADHD, the treatment should not be changed (dosage, timing, class of drug), during the study period.

Exclusion: Children with visual impairment, current psychotic symptoms, suicidal ideations or behaviour are excluded from the study.

### Measures

*ADHD-RS* [18]: The questionnaire is parent- and teacher reported and is used to assess the severity of core symptoms of ADHD (inattention, hyperactivity, and impulsivity). The questionnaire is widely used to evaluate change before and after initiation of a treatment. The version translated into Danish is the ADHD-RS-IV, a modified version consisting of 26 items, reflecting three subscales: Inattention (9 items), Hyperactivity/impulsiveness (9 items) and behavioural difficulties (8 items) [19]. In this trial, the total score is based on the 18 items measuring inattention and hyperactivity/impulsiveness (total score of 0–54).

*SDQ - Strengths and Difficulties Questionnaire* [20]: The questionnaire consists of five subscales: 1) Hyperactivity/inattention, 2) Emotional issues, 3) Behavioural issues, 4) Issues in relation to peers 5) Social strengths. The version with 25 items for parents and teachers is applied [21].

*KIDSCREEN-27* [22]: The self-report questionnaire for children focuses on health-related quality of life in children and young people aged 8–18. The questionnaire consists of five dimensions: 1) Physical wellbeing (5 items), 2) Psychological well-being (7 items), 3) Autonomy and parental relations (7 items), 4) Friends and social support (4 items), and 5) School environment (4 items). The questionnaire consists of 27 statements. It is recommended that the children complete the questionnaire during regular school hours in the presence of a teacher, or other adult, with whom the child is familiar, so that he or she can assist the child, if necessary.

*Qb Test* [23]: The Qb Test is a computer-test combining infrared camera recordings of the child’s movements, with a concurrent computer test, a *Continued Performance Test,* which measures the child’s attention and impulse control. The Qb Test produces quantitative measurements of difficulties in the three areas, characterizing the core symptoms of ADHD; inattention, hyperactivity and impulsiveness. The test has previously been proven valid and sensitive, in the monitoring of the effect of pharmacological treatment of children and young people’s ADHD core symptoms [23, 24].

*Semi-structured interviews *[25, 26]: The interviews focus on the participants’ experiences, reflections and impressions, regarding the period of intervention, as well as everyday life, in order to assess the influence of target-shooting sport for children with inattentive, hyperactive and impulsive symptoms. The interviews follow manuals, developed by the research team for each target group (parents, children, school staff and target shooting sport instructors). All participants are encouraged to speak freely and raise additional issues of importance. All interviews are audiotaped and transcribed verbatim. The interviews are analysed, in accordance with the descriptive phenomenological psychological method [26].

*Observations* [25]: Observations of participating children will be carried out in schools and during practise at the local shooting association, The observations are videotaped, if possible. An observation sheet developed especially for this study is used to guide and structure the observations.

#### Outcomes

The primary outcome is:The total score on the 18 items on symptoms of inattention, hyperactivity and impulsivity on the teacher-rated ADHD-RS-IV.

Secondary outcomes are:Hyperactivity (distance and area) and inattention (reaction time variance and omission errors) as measured by the Qb Test.The total score on the relevant 18 items on symptoms of inattention, hyperactivity and impulsivity on the parent-rated ADHD-RS-IV.The total scores on the teacher- and parent-rated SDQ.Quality of life as measured by the total score on the child-rated Kidscreen-27.

Interviews and observations will add to a phenomenological understanding of children’s participation and engagement in their daily life and will qualify to an in-depth understanding of the mechanisms of change.

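### The only quantitative outcome left for the comorbidity objective is the SDQ total, and the SDQ includes a hyperactivity/inattention subscale, so a favourable total cannot isolate comorbid symptoms

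*Protocol article*

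**What the plan says.** The Objectives section of the protocol article gives core symptoms one entry, "Inattention, hyperactivity, and impulsiveness", and comorbidity another, "Comorbid symptoms, such as emotional, social and behavioural difficulties". The hypothesis keeps them apart too: the intervention is expected to reduce "symptoms of inattention, hyperactivity and impulsivity, their comorbid symptoms, and enhance their wellbeing".

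The Measures section describes the SDQ as five subscales, "1) Hyperactivity/inattention, 2) Emotional issues, 3) Behavioural issues, 4) Issues in relation to peers 5) Social strengths", and adds that "The version with 25 items for parents and teachers is applied". It does not say which subscales form a total.

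The Outcomes section makes the 18-item teacher-rated ADHD-RS-IV score the primary outcome. The secondary outcomes are four Qb Test measures of hyperactivity and inattention, the same 18-item score rated by parents, "The total scores on the teacher- and parent-rated SDQ", and the Kidscreen-27 total for quality of life. No SDQ subscale is named.

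**The concern.** The plan treats comorbid difficulties as a domain of their own and expects an effect there beyond any effect on ADHD symptoms. The score that has to show this contains, as one component, the domain of the primary outcome. If the intervention eased hyperactivity and inattention and changed nothing else, the expected SDQ total would still fall.

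This matters because comorbidity is one of three stated objectives, and because the overlap is greatest when the intervention works as hypothesised on ADHD symptoms. Teachers rate both the primary outcome and one version of the SDQ, and the study is not blinded. A shift in how a teacher sees a child's restlessness can therefore appear on both instruments.

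**Working it through.** The plan states no figure on this point, so there is none to reproduce. The check traces objective to outcome and then illustrates the size.

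**Step 1: which outcome can serve the comorbidity objective?**

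| Quantitative outcome | What it covers |
|---|---|
| Teacher ADHD-RS-IV, 18 items (primary) | Core ADHD symptoms |
| Parent ADHD-RS-IV, 18 items | Core ADHD symptoms |
| Qb Test: distance, area, reaction time variance, omission errors | Hyperactivity and inattention |
| Kidscreen-27 total | Quality of life |
| SDQ total, teacher and parent | Mixed, including comorbid domains |

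The Danish ADHD-RS-IV also has 8 behavioural items, but the Measures section leaves them out: "In this trial, the total score is based on the 18 items measuring inattention and hyperactivity/impulsiveness". Interviews and observations are qualitative. Only the SDQ total remains.

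**Step 2: what is in that total?** The four difficulty subscales are hyperactivity/inattention, emotional, behavioural and peer. If the 25 items are split equally over five subscales (an assumption), each has 5 items. Hyperactivity/inattention then supplies 5/20 = 25% of a four-subscale total. A change of one point on it changes the total by one point, with the other subscales held still.

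**Step 3: how large could the effect be? (illustration only)**

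From the section on sample size and statistical analyses: means 32.3 and 24.2, so a difference of 8.1; SDs 10.2 and 15.2; 50 enrolled per group; 20% dropout, so 50 × 0.80 = 40 per group; two-sided 5%.

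Assumptions not in the documents:
- The planned standardised ADHD-RS effect carries over in full to the SDQ hyperactivity/inattention subscale, and all other subscales stay at zero.
- Subscales have equal SDs and a common pairwise correlation ρ of 0 to 0.5.
- The total has k = 4 subscales, or k = 5 with social strengths scored in the same direction as the rest.
- Two means are compared by the normal approximation, without baseline adjustment or clustering.

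Effect on the subscale: d_h = 8.1/15.2 = 0.53; 8.1/12.7 = 0.64 (12.7 being the plain average of the two SDs); 8.1/10.2 = 0.79.

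Effect on the total: d_total = d_h / √(k + k(k−1)ρ).

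Chance of a favourable significant result: Φ(d_total·√(n/2) − 1.96).

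| k | ρ | d_h | d_total | n = 40 per group | n = 50 per group |
|---|---|---|---|---|---|
| 4 | 0 | 0.79 | 0.395 | 42.3% | 50.6% |
| 4 | 0 | 0.53 | 0.265 | 21.9% | 26.3% |
| 4 | 0.3 | 0.64 | 0.232 | 17.8% | 21.2% |
| 4 | 0.5 | 0.53 | 0.168 | 11.3% | 13.1% |
| 5 | 0 | 0.79 | 0.353 | 35.2% | 42.3% |
| 5 | 0.5 | 0.53 | 0.137 | 8.9% | 10.1% |

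Worked line, k = 4, ρ = 0.5, d_h = 0.53: 0.53/√(4 + 12 × 0.5) = 0.53/3.162 = 0.168; 0.168 × √20 − 1.96 = −1.21; Φ = 0.113.

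A score without the hyperactivity/inattention subscale has d = 0 in this scenario, so the favourable chance is 2.5% per rater.

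**The case against.** Several counter-arguments have force.

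- **The link is inferred.** The article never says that the SDQ total tests comorbidity; it lists outcomes without assigning them to objectives. That stands as a limit on wording. The elimination in Step 1 is nonetheless complete for the quantitative outcomes named.
- **The total is mostly on target.** Three of the four difficulty subscales are emotional, behavioural and peer, about 75% if equally long. A reader might infer that the total cannot address the comorbidity objective at all. That is not supported: the total would respond to a real change in those domains. What it cannot do is separate such a change from a core-symptom change.
- **Significance is not assured.** A reader might infer that an ADHD-only effect would count as improved comorbidity. With 40 per group, every scenario shown leaves significance less likely than not, and the figures rest on assumptions outside the documents. The supportable word is could.
- **Social strengths.** A reader might infer that adding this subscale, where more is better, would cancel gains elsewhere. The documents do not say that the total includes it, so nothing is claimed on this.
- **Planned data could settle it.** The ADHD-RS and Qb Test measure core symptoms separately, and an article may leave subscale reporting to a fuller document. This helps a careful reader interpret the result. It does not remove the point, because the article fixes the outcome as the total; the issue is what was chosen, not a missing detail.
- **A total is a legitimate choice.** Agreed, as a measure of overall difficulties. The objection is only to its being the sole quantitative comorbidity outcome.

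**Conclusion.** The point holds as a mismatch between a stated objective and a stated outcome. A favourable SDQ total could come from comorbid symptoms, from core ADHD symptoms or from both, and the outcome as defined cannot tell these apart.

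The structural conclusion rests on the article's text plus the elimination in Step 1, and requires only that the SDQ total contains the hyperactivity/inattention subscale. The sizes of 0.14 to 0.40 SD, and about 9% to 42% per rater with 40 per group (10% to 51% with 50), illustrate the possible scale and are not properties of this plan.

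The consequence is limited. The primary outcome, the sample size and the main conclusion are untouched, and the authors themselves call for larger randomised trials if the intervention looks effective. It is still worth correcting, because the remedy uses data already being collected.

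**What to change.** In the Outcomes section:

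- Name the teacher- and parent-rated SDQ emotional, behavioural and peer subscales as the secondary outcome for the comorbidity objective, either separately or as one sum without hyperactivity/inattention.
- Analyse social strengths separately.
- Keep the SDQ total as a supporting outcome, state which subscales form it, and label it as overlapping with the primary outcome.

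This takes one line in the outcome list and needs no new questionnaires, visits or children. A three-subscale sum is shorter and may be less reliable than the full total, and the documents give nothing on its measurement properties. Separate subscales avoid the composite but add a few secondary comparisons.

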### The intervention

The intervention is organised in collaboration with DGI Shooting, local schools, local shooting associations and the University of Southern Denmark. The intervention is carried out nationwide in Denmark. The children attend the shooting range for about 1 h, practicing rifle shooting, once a week, for a period of six months. Teachers accompany the children to the local shooting associations, where their shooting instructors meet them. Before the shooting session there is formal introduction and preparation. Every child shoots approximately 20 to 30 min. As part of each training session, participating children meet up in the club’s common room after the shooting session, where the children receive feedback before going back to school, with their teachers.

### Safety procedures

Due to regulations in the Danish Shooting Associations, riffles are kept in a locked weapons storage cabinet, which requires two separate keys to open. Only members of the Shooting Association, who hold permission from the police, hold the keys for the weapons cabinet. The riffles are never allowed to leave the club area, and throughout the shooting practice an individual, responsible adult instructor will monitor and watch each child, at all times.

### Procedures

The participating schools identify, which children are eligible to enrol in the study. Participating children are not randomized, but included either to an intervention group or to a waiting list control group, as they are identified. Waiting list control children are recruited from schools that agree to participate in the study, but will not be part of the intervention until after study period. The children in the waiting list control group have the same characteristics as the children in the intervention group, but are not practicing target-shooting sport during the study period. Parents of all eligible children receive verbal and written information about the intervention, following the guidelines of the National Committee on Health Research Ethics. Upon parental consent, the teacher informs and provides written information to the child. The written information will be read out loud and explained to the child. Background information (including diagnosis, use of medication and participation in leisure time activities) are provided by parents one week prior to the intervention, three months into the intervention and 6 months post intervention. ADHD-RS-IV, SDQ, and KIDSCREEN-27 questionnaires are collected one week prior to the intervention. Data, from the waiting list control group, will be collected at the same time. Questionnaires will be distributed to parents and teachers. The children will fill out the questionnaire (Kidscreen-27) and complete the computer test (Qb Test) during regular school hours. A research assistant will carry out the Qb Test at the participating schools.

The multiple case study, combining interviews and observations, is nested in the quantitative survey adding substantial in-depth information. Children, parents, teachers and shooting instructors will be interviewed during the intervention. The interviews will mainly focus on experiences with the intervention and changes in quality of life and wellbeing for the children. Interviews with the children, teachers and parents will be carried out either at the school or at the child’s home address. Interviews with shooting instructors will take place in the local shooting associations. The first author will conduct and record all interviews.

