### Sample size and statistical analyses

Sample size calculations are based on the following parameters: The total score of the first 18 items of ADHD-RS-IV is the primary outcome measurement. In a validation study of a Danish clinical sample of 10–17-year-old boys with ADHD, the mean total-score was 32.3 (standard deviation (SD) 10.2) [27]. With an effect of the intervention on this outcome with a 25% reduction in the total score (=24.2) and with an expected SD of 15.2), a power of 80%, 1:1 allocation in the two groups, two-sided testing and a significance level of 5%, a total sample of 78 is required. In an evaluation of the sport project preceding this study [15] the dropout rate from participation in target shooting sport was below 15%. Following these parameters and a more conservative expected dropout at 20% it is estimated that there should be 50 children enrolled in each group. The following online statistics programme has been used for the calculation: http://www.quantitativeskills.com/sisa/calculations/samsize.htm. The primary and secondary outcomes measured for both groups, pre- and post-intervention will be analysed using linear mixed-effects models (random coefficient models and multilevel models). With the mixed effects model approach, all available data will be used and intention-to-treat analyses applied. A thematic analysis [26] will be made separately for each case, followed by an analysis across all cases to investigate common themes and patterns [17]. The number of cases enrolled will depend on when data-saturation is reached.

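### Group largely follows school, but the sample size treats children as independent, so the stated 80% power is overstated for any positive within-school correlation

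*Protocol article*

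**What the plan says.** Under Procedures, the protocol article states that children are not randomised and describes where the controls come from: "Waiting list control children are recruited from schools that agree to participate in the study, but will not be part of the intervention" until the study period is over. A control school therefore supplies only controls during the study. Under The intervention, "Teachers accompany the children to the local shooting associations, where their shooting instructors meet them", so treated children from one school also share a local club. Under Outcomes, the primary outcome is the 18-item ADHD-RS-IV total as rated by the teacher.

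Sample size and statistical analyses bases the calculation on a validation sample in which "the mean total-score was 32.3 (standard deviation (SD) 10.2"), an effect of "a 25% reduction in the total score (=24.2"), an expected SD of 15.2, "a power of 80%, 1:1 allocation in the two groups", and a two-sided 5% test. The result is 78 children in total, raised to 50 per group for 20% dropout. The listed inputs contain no ICC, number of schools, children per school or design effect. The analysis is described as "linear mixed-effects models (random coefficient models and multilevel models"), with no statement of which levels enter.

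**The concern.** Children in the same school share a setting, possibly a rater and, in the intervention group, a shooting club. Their scores, and their changes in score, are likely to be correlated. When group is tied to school, that correlation inflates the variance of the group contrast. A two-sample calculation on independent children ignores this and so promises more power than the design can give.

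The calculation is completed in the article and is not deferred to an analysis plan, so this is a mismatch between the stated design and the stated calculation. The analysis wording is a secondary matter. A model of occasions within children would satisfy it while ignoring school, and the standard error would then be too small. At stake are the credibility of the 80% claim and, depending on the model finally used, the validity of the primary test.

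**Working it through.** **Inputs from the article:** difference 32.3 − 24.2 = 8.1 points; SD 10.2 (observed) or 15.2 (expected); two-sided 5%; 80% power; 1:1 allocation; 78 in total; 50 enrolled per group, so 50 × 0.8 = 40 analysable.

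**Assumed, because the article gives neither:** children per school m = 5 to 10, and ICC = 0.05 to 0.15 for the score actually analysed.

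**Step 1, the plan's own figure.** n per group = 2 × (SD × (1.96 + 0.84) / 8.1)².
- SD 15.2 gives 55.3, so 56 per group and 112 in total.
- SD 10.2 gives 24.9, so 25 per group and 50 in total.
- SD 12.7 gives 38.6, so 39 per group and 78 in total.

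The 78 does not follow from the stated SD of 15.2. It corresponds to a common SD of about 12.7. This is a separate error. To keep it out of the clustering loss, the steps below use SD 12.7 (which returns 78) and SD 10.2 (the only observed value). The dropout step is consistent: 78 / 0.8 = 97.5, rounded up to 100.

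**Step 2, design effect.** DE = 1 + (m − 1) × ICC.
- m = 5, ICC 0.05: 1 + 4 × 0.05 = 1.20
- m = 8, ICC 0.10: 1 + 7 × 0.10 = 1.70
- m = 10, ICC 0.15: 1 + 9 × 0.15 = 2.35

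**Step 3, sample size.** 78 × 1.20 = 93.6, 78 × 1.70 = 132.6 and 78 × 2.35 = 183.3. The requirement is thus about 94 to 183 analysable children, against about 80 planned.

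**Step 4, power at 40 per group.** Power = Φ(8.1 / (SD × √(2 × DE / 40)) − 1.96).

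| DE | SD 12.7 | SD 10.2 |
|---|---|---|
| 1.00 | 81% | 94% |
| 1.20 | 74% | 90% |
| 1.70 | 59% | 78% |
| 2.35 | 46% | 64% |

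For example, at SD 12.7 and DE 1.20: 8.1 / (12.7 × √0.06) = 2.60, and Φ(2.60 − 1.96) = 0.74. At SD 10.2, power reaches 80% at DE = 40 / 24.9 = 1.61.

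**Step 5, credit for baseline.** Assume a pre-post correlation of 0.6 that acts equally at child and school level. The residual variance is then 1 − 0.36 = 0.64 of the original, so SD 12.7 becomes 12.7 × 0.8 = 10.2. Power is then close to the right-hand column: 90% at DE 1.20 and 64% at DE 2.35.

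**Step 6, type I error if school were left out of the model.** α = 2 × (1 − Φ(1.96 / √DE)): 7.4% at DE 1.20, 13.3% at 1.70 and 20.1% at 2.35.

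Steps 4 to 6 use the normal approximation. With 80 analysable children there would be only 80 / 10 = 8 to 80 / 5 = 16 schools, so a proper small-sample test would have somewhat less power than shown.

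**The case against.** The best defence is that multilevel models are named. In a school-based study that phrase ordinarily suggests a cluster level, and a condensed article may leave the levels to an analysis plan that is not shown. This stands as far as it goes. A reader might infer that the primary test is anti-conservative, but the article does not say that school will be omitted, so the 7% to 20% is conditional. It does not rescue the sample-size calculation, which is complete in the article and has no clustering term.

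A second objection is that power may still be adequate. This also stands in part. A reader might infer that 80% is out of reach at the planned size. The figures do not support that: at the observed SD of 10.2, power stays at 80% or more up to a design effect of about 1.6, and baseline adjustment could do much the same at SD 12.7. The stated calculation, however, claims no credit for baseline.

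Third, where the same teacher rates a child before and after, stable leniency cancels from the change. That is correct, and it is why the relevant ICC is that of the adjusted or change score. Schools that change differently over time still contribute.

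Two further readings go beyond the text. Random coefficient models might be taken to mean a child-level random slope, which two occasions could not identify, but no such slope is stated. Nor does the article say how many children one teacher rates, so a separate teacher level cannot be required.

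**Conclusion.** The point holds for the sample size. Controls come from schools that do not deliver the intervention during the study, yet the calculation counts children as independent. Its 80% power at 78 is therefore overstated, on its own terms, for any positive within-school correlation of the score analysed. The direction is certain for any such correlation. The size is not, because it depends on an ICC and a school size that are assumed here; the upper end pairs the largest values of both. Over the assumed range, the loss at SD 12.7 runs from about 7 percentage points (81% to 74%) to about 35 (81% to 46%).

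A reader might add the figures at SD 15.2 as further evidence of clustering loss. They are not: at that SD, power at 40 per group is already 66% with independent children, because 78 does not follow from 15.2.

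The article states that intervention is withheld at control schools but does not say outright that intervention schools supply no controls, so group follows school largely rather than provably in every case.

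**What to change.** 1. Reconcile 78 with the stated SD first, so that the base figure is right before any design effect is applied.
2. Keep enrolment at 50 per group. Restate the power for 40 analysable per group over a stated range of ICCs and children per school, with and without baseline adjustment, and give the expected number of schools.
3. Write down the primary model: the post-intervention teacher-rated total, adjusted for its baseline value, with a random intercept for school. If a repeated-measures model is preferred, include a school-by-time random effect as well as a child effect. A constant school intercept alone largely cancels from the change contrast and would leave the problem in place.
4. Use small-sample degrees of freedom suited to the number of schools, for example Kenward-Roger.

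The cost is wording, a school identifier in the dataset, a wider confidence interval and a lower stated power. No extra children are needed. The change corrects the standard error; it does not remove confounding from the non-random allocation of schools, which should be acknowledged when the result is reported.
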